**Data collection**					
Written informed consent	□				
Inclusion/exclusion criteria	□				
Demographics	□				
Obtain central random number	□				
Previous history, medical history, and allergies	□				
Comorbidities and co-medications	□	□	□	□	□
Safety evaluation					
Vital signs and physical examination	□	□	□	□	□
Blood routine, Urine routine, Fecal routine	□		□	□	
Liver function(ALT, AST, ALB), kidney function(UN, Cr, UA, eGFR)	□		□	□	
12-Lead ECG	□		□	□	□
Efficiency evaluation					
Composite outcome measures	□	□	□	□	□
Preset exploration indicators	□	□	□	□	□
BMI, waist to hip ratio, body fat analysis	□	□	□	□	□
Blood glucose, blood lipids, blood pressure	□		□	□	□
Fasting insulin, C-peptide, HOMA-IR	□		□	□	□
Cardiovascular and cerebrovascular risk index	□		□	□	□
Troponin, cardiac enzymes, BNP	□		□	□	□
Vitamin D	□			□	□
UACR	□		□	□	□
Cardiac color doppler ultrasound	□			□	□
Neck vascular ultrasound	□			□	□
Traditional chinese medicine syndrome points	□	□	□	□	□
Quality of life rating	□	□	□	□	□
Omics analysis	□			□	

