### Secondary outcomes

Metabolic and anthropometric parameters: blood glucose, lipids, blood pressure, BMI, waist-to-hip ratio, HOMA-IR, body composition analysis, Vitamin D.Vascular and cardiac assessments: peripheral vascular status, myocardial status (left ventricular thickness, interventricular septum thickness), cardiovascular risk assessment indices (China-PAR score, Framingham Risk Score, QRISK3 score).TCM symptom score and quality of life scores.

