### Sample size calculation

This is a two-arm, randomized, controlled superiority trial with a placebo control group and a TJC group. Using the composite primary outcome measure and a superiority test for proportions for sample size estimation. Based on literature, the estimated difference between the two groups is 15% (27, 38). With a one-sided *α*=0.025 and power (1-*β*) of 90%, using PASS 15 software for a 1:1 allocation ratio, and accounting for a potential 20% dropout rate (due to loss to follow-up, refusal, exclusion, etc.), a minimum of 265 subjects per group is required, resulting in a total sample size of at least 530 subjects.

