### Statistical analysis

A detailed statistical analysis plan (SAP) will be finalized before database lock and unblinding. Statistical analyses will be performed using SAS version 9.4 (SAS Institute Inc., Cary, NC, USA) by the statistics department of the Clinical Research Center at Guangdong Provincial Hospital of Traditional Chinese Medicine. Data from all randomized patients will be analyzed according to the Intent-to-Treat (ITT) principle. Consistent with the CONSORT statement and ITT principle, the last observation carried forward (LOCF) method will be used to handle missing data for the primary analysis.

① Hypothesis Testing: All statistical tests will be two-sided, with a *p*-value less than 0.05 considered statistically significant.② Statistical Description: Normally distributed continuous variables will be described using “mean ± standard deviation,” non-normally distributed continuous variables using “median (interquartile range),” and categorical data using frequencies and percentages.③ Choice of Statistical Methods: Appropriate statistical methods will be selected based on the nature of the data (continuous, categorical, ordinal). Categorical data will be compared using the Chi-square test or Fisher's exact test. For continuous data meeting normality and homogeneity of variance assumptions, the t-test will be used for between-group comparisons; otherwise, the Wilcoxon rank-sum test will be employed. Ordinal data between two groups will be compared using the Mann–Whitney U test, and for multiple groups, the Kruskal–Wallis test. The center effect in the multi-center efficacy evaluation will be analyzed using the Cochran-Mantel-Haenszel method.④ Statistical Analysis Steps: The statistician will follow the pre-specified SAP, meticulously check and confirm the clinical trial data, and then proceed with the statistical analysis. This will include descriptive statistics, baseline comparison of clinical characteristics before treatment, efficacy analysis, safety evaluation, and analysis of excluded and dropped-out cases. If potential confounding factors that are difficult to fully control or were not controlled (e.g., age, disease severity, duration) are imbalanced between groups at baseline, analysis of covariance (ANCOVA) will be used to analyze the impact of these factors on the between-group differences in efficacy, thereby adjusting for the influence of confounders.

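### Continuous secondary outcomes measured at up to five visits are assigned two-sample tests, with the reach of LOCF unclear; either reading can bias the comparison, and a repeated-measures model would use all visits

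*Protocol article*

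**What the plan says.** The Statistical analysis section of the protocol article, item 3, assigns tests by data type. For continuous outcomes meeting normality and equal-variance assumptions, "the t-test will be used for between-group comparisons; otherwise, the Wilcoxon rank-sum test will be employed". The only model named is in item 4 and is conditional: if factors such as age or severity "are imbalanced between groups at baseline, analysis of covariance (ANCOVA) will be used".

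The same section says "Data from all randomized patients will be analyzed according to the Intent-to-Treat (ITT) principle" and that "the last observation carried forward (LOCF) method will be used to handle missing data for the primary analysis". It gives no separate missing-data rule for secondary outcomes.

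The Secondary outcomes section lists "Metabolic and anthropometric parameters: blood glucose, lipids, blood pressure, BMI, waist-to-hip ratio, HOMA-IR, body composition analysis, Vitamin D", together with cardiac and vascular measures, risk scores, TCM symptom score and quality of life. Table 1 schedules them as follows:

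- Five visits (baseline, weeks 4, 12, 26, 52): "BMI, waist to hip ratio, body fat analysis", TCM score, quality of life.
- Four visits (no week 4): "Blood glucose, blood lipids, blood pressure", HOMA-IR, cardiovascular risk indices.
- Three visits (baseline, weeks 26 and 52): vitamin D, cardiac and neck vascular ultrasound.

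The Sample size calculation reaches 265 per group after "accounting for a potential 20% dropout rate".

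**The concern.** The stated method does not match the stated data structure. A t-test or rank-sum test compares one value per patient and cannot use the other visits. What happens to patients who leave therefore depends entirely on the missing-data rule, and for the secondary outcomes that rule is unclear. Without LOCF, those missing at a visit drop out of its comparison. With LOCF, an earlier measurement is treated as if taken later.

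The Study objectives section makes improved glycolipid metabolism part of the hypothesis, and the Discussion presents the secondary outcomes as the metabolic and vascular steps leading to events. If poorly controlled patients leave the placebo arm more readily than the TJC arm, the remaining placebo patients look better than that arm really was and a true effect is understated. The reverse pattern overstates it.

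**Working it through.** **Inputs from the article.** 265 per arm; 20% planned dropout; visits as in Table 1. If all the dropout fell before a visit, 265 × 0.80 = 212 per arm would be seen and 53 per arm would not. The 265 itself cannot be reproduced because no event rates are given, but nothing here depends on it.

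**Assumptions (the article gives none of these).** Outcome SD 1. Correlations: baseline–week 12 0.60, baseline–week 26 0.55, week 12–week 26 0.70. True effect (positive = benefit) 0.10 SD at week 12 and 0.25 SD at week 26. Dropout lies between weeks 12 and 26 and its log-odds rise with a worse week-12 value: by 0.9 per SD on placebo and 0.3 on TJC when the arms differ, by 0.6 in both when they do not.

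**Reading 1: LOCF does not apply, patients seen at week 26 only.** For a standard normal week-12 value and logistic dropout with slope g and overall rate d, the week-26 mean of those who stay shifts by

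ρ × g × E[p(1−p)] / (1−d), with ρ = 0.70.

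E[p(1−p)], by numerical integration at d = 0.20, is 0.142 for g = 0.9 and 0.158 for g = 0.3:

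- Placebo: 0.70 × 0.9 × 0.142 / 0.80 = 0.112.
- TJC: 0.70 × 0.3 × 0.158 / 0.80 = 0.041.
- Bias: 0.112 − 0.041 = 0.07 SD, so 0.25 is estimated as about 0.18.

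At d = 0.10 the corresponding averages are 0.083 and 0.089: 0.70 × 0.9 × 0.083 / 0.90 − 0.70 × 0.3 × 0.089 / 0.90 = 0.058 − 0.021 = 0.037, about 0.04 SD. With the same g and d in both arms the two shifts cancel.

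**Simulation of the same settings.**

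| Setting | Analysis | Mean estimate (true 0.25) | Power | Type I error |
|---|---|---|---|---|
| 20% lost, link differs | t-test, patients seen | 0.18 | 46% | 11% |
| 20% lost, link differs | ANCOVA, patients seen | 0.21 | – | – |
| 20% lost, link differs | repeated-measures ML | 0.25 | 89% | 5% |
| 10% lost, link differs | t-test, patients seen | 0.21 | – | 7% |
| 20% lost, link equal | t-test, patients seen | 0.25 | 75% | 5% |
| 20% lost, link equal | ANCOVA, patients seen | 0.25 | 88% | – |
| 20% lost, link equal | repeated-measures ML | 0.25 | 89% | – |

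**Reading 2: LOCF applies.** With 20% lost at random after week 12, the expected estimate is 0.80 × 0.25 + 0.20 × 0.10 = 0.22 SD. A second set of runs, with true effect 0.3 SD and half of it present at week 12, gives 0.80 × 0.30 + 0.20 × 0.15 = 0.27.

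**Sensitivity to the mechanism.** In that second set, with 20% lost and correlation 0.5 to 0.7, only control-arm dropout was made to depend on response. The t-test on patients seen was then off by 0.09 to 0.12 SD (type I error 15% to 26%). The LOCF t-test was off by 0.04 to 0.07 SD in the opposite direction (8% to 13%). The likelihood-type estimate stayed within about 0.01 SD. Where one common dropout rule applied in both arms and the drug worked, the bias on patients seen was only 0.01 to 0.04 SD.

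**The case against.** A reader might infer that the plan analyses completers at week 26 and throws away leavers' earlier data. The article does not say so. It commits to all randomized patients under ITT, names no time point for the secondary outcomes, and may intend LOCF to cover them, in which case an earlier value is kept. That stands, which is why both readings are worked through.

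A reader might also infer that any response-dependent dropout biases the comparison. It does not: the bias nearly cancels when the link is the same in both arms. The trial is double-blind with matched placebo and standard care in both arms, and the article does not state that the link differs. The Withdrawal criteria do tie leaving to concomitant-medication violations, and the Discussion reports mainly gastrointestinal discomfort on TJC. Different reasons for leaving are therefore plausible, but that is an inference.

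The 20% is a whole-study allowance for sizing the primary composite, covering refusal and exclusion as well as loss, so loss before week 26 may be smaller. Most of the power gain belongs to baseline adjustment: with equal dropout, 13 of the 14 points (75% to 88% to 89%).

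Finally, a detailed SAP is still to come, and a protocol article may leave the longitudinal model to it. But the article is not silent here: it names a test, and that test is a weak choice for these data. The point is a better method than the one stated, not a request for missing detail.

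**Conclusion.** The concern holds in a limited form. The article assigns two-sample tests to continuous secondary outcomes mostly measured at four or five visits, and leaves it unclear whether LOCF covers them. Without LOCF, a single-visit comparison can be biased by about 0.07 SD (type I error about 11%) at 20% loss, or about 0.04 SD (7%) at 10%, but only if the response–dropout link differs between arms; otherwise the bias is near zero. With LOCF, an effect that grows over time is diluted, 0.22 for 0.25 SD here, even under random dropout. The SDs, correlations, effects and dropout mechanisms are assumptions, so these sizes are illustrative. The primary endpoint is not touched. Since neither reading is safe and the remedy is cheap, the change should be made before the SAP is finalized.

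**What to change.** For continuous secondary outcomes with at least two post-baseline visits, make the main analysis one mixed model for repeated measures: treatment, visit, treatment-by-visit, baseline value, baseline-by-visit and centre, with unstructured covariance, all observed visits and no LOCF. Log-transform skewed variables. Report the end-of-treatment (week 26) contrast with its 95% CI, keep the rank test as a sensitivity analysis, and state that LOCF does not apply to these outcomes.

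The cost is protocol and SAP wording and modest programming in the SAS already planned, with no new data or patients. The downside is reliance on missing-at-random dropout, which a sensitivity analysis should probe. Vitamin D and the ultrasound measures have no on-treatment visit before week 26, so for them the gain at that visit is little more than baseline adjustment.

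### Patient covariates are adjusted for only when found imbalanced, and continuous outcomes have no stated adjustment for their baseline value; the tests stay valid, but covariate choice depends on the data and precision is lost

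*Protocol article*

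**What the plan says.** All the rules are in the Statistical analysis section of the protocol article, items 3 and 4.

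- Continuous data: if normality and equal-variance assumptions are met, "the t-test will be used for between-group comparisons; otherwise, the Wilcoxon rank-sum test will be employed". No covariate is named.
- Categorical data: "Categorical data will be compared using the Chi-square test or Fisher's exact test".
- Centre: "The center effect in the multi-center efficacy evaluation will be analyzed using the Cochran-Mantel-Haenszel method". No imbalance condition is attached.
- Other factors: item 4 lists a "baseline comparison of clinical characteristics before treatment" among the analysis steps. The rule that follows covers uncontrolled factors that "are imbalanced between groups at baseline, analysis of covariance (ANCOVA) will be used to analyze the impact of these factors". They are given as examples only ("e.g., age, disease severity, duration"), no test or threshold for imbalance is stated, and the adjustment is aimed at efficacy in general, without restriction to continuous outcomes.

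The Secondary outcomes section lists glucose, lipids, blood pressure, BMI, HOMA-IR and others. Table 1 schedules "Blood glucose, blood lipids, blood pressure" at baseline and at weeks 12, 26 and 52, and BMI also at week 4. The baseline values needed for adjustment will therefore be in the database.

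**The concern.** After randomisation, a baseline difference between arms is chance. Whether a covariate belongs in the model depends on how strongly it predicts the outcome, not on how far the arms happen to differ. A rule triggered by imbalance selects on the wrong property, and it can be applied only once the data have been split by arm. With no criterion and an open list, two analysts could follow the text faithfully and report different adjusted results.

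The second issue is efficiency. For a measure such as fasting glucose or blood pressure, the patient's own baseline value is usually among the strongest predictors of the later value. Leaving it out unless it looks imbalanced forgoes precision that costs nothing to obtain.

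**Working it through.** **What the document supplies.** It gives no figure for this point: no standard deviation, effect size or baseline-outcome correlation for any secondary outcome. From Sample size calculation, 265 per arm with 20% dropout leaves 265 × 0.8 = 212 per arm. The correlation r is assumed, from 0.3 to 0.8.

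**Precision.** Let the outcome have variance σ² at baseline and at follow-up. The per-patient variance of the treatment comparison is proportional to:

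- follow-up value, unadjusted: σ²
- change from baseline: 2σ²(1 − r)
- ANCOVA on the baseline value: σ²(1 − r²)

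The variance of ANCOVA is therefore 1 − r² relative to follow-up values, and (1 − r²) / [2(1 − r)] = (1 + r)/2 relative to change scores. The SE ratio is the square root; the equivalent gain in patients is 1/factor − 1.

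| r (assumed) | Factor vs follow-up | SE cut | Equivalent gain | Factor vs change | SE cut | Equivalent gain |
|---|---|---|---|---|---|---|
| 0.3 | 0.91 | 5% | 10% | 0.65 | 19% | 54% |
| 0.5 | 0.75 | 13% | 33% | 0.75 | 13% | 33% |
| 0.7 | 0.51 | 29% | 96% | 0.85 | 8% | 18% |
| 0.8 | 0.36 | 40% | 178% | 0.90 | 5% | 11% |

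For example, at r = 0.7: √0.51 = 0.714, so the SE falls by 29% against follow-up values; √0.85 = 0.922, so it falls by 8% against change scores. There is some gain against follow-up values for any r above 0, and against change scores for any r below 1.

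**What the trigger does.** A simulation used 212 per arm, one baseline covariate, 20,000 trials per setting, and an unadjusted t-test on follow-up values. Because the plan sets no criterion, imbalance was taken as p < 0.05 on the covariate, and the effect as 0.25 SD (both assumed).

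| Two-sided 5% test | r = 0.5 | r = 0.7 |
|---|---|---|
| Power, adjust only if imbalanced | 74% | 74% |
| Power, ANCOVA always | 84% | 95% |
| Type I error, fixed trigger | 0.042 | 0.038 |
| Type I error, better of adjusted and unadjusted result | 0.069 | 0.085 |

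The trigger recovers almost none of the available power, because it fires in only about 5% of trials: the formula gives 73% for the test that never adjusts. A fixed trigger on one covariate is slightly conservative. Type I error rises only if the missing criterion is used to pick between results.

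**The case against.** Several parts of the defence stand.

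- A reader might infer that nothing is adjusted for unless imbalanced. That is not so: centre is handled by Cochran-Mantel-Haenszel without condition.
- A reader might infer that ANCOVA, a model for continuous outcomes, will be fitted to 3P-MACE. The text applies it to efficacy without restriction and names no event model, but it never says this, and item 3 ties the choice of method to the type of data. The sentence needs its scope stated; it is not a declared misuse.
- A reader might infer that the tests ignore baseline altogether. The article does not say whether follow-up values or changes are tested, and a change score does use the baseline. Against change scores the gain at r = 0.7 is much smaller (8%, not 29%).
- A reader might infer inflated type I error. The article commits to an analysis plan finalised before the arms are revealed and to following it, and nowhere permits choosing between results. With a fixed trigger the simulated error is below 5%.
- A reader might argue that the secondary outcomes are where this trial has its power. The document gives nothing from which to judge that.

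The trigger also has an honest motive. In the simulated null trials where the covariate was imbalanced at p < 0.05, the unadjusted test rejected 17% (r = 0.5) or 35% (r = 0.7) of the time. Adjusting always deals with this as well, without looking at the imbalance first.

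The defence fails on one point. That the analysis plan may add detail does not rescue the rule, because the rule is stated here. A plan could supply a criterion and a list, but as long as the trigger stands, the observed arms decide which covariates enter.

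**Conclusion.** The point holds as one of efficiency and pre-specification, not of validity. The article fixes an imbalance-triggered adjustment with no criterion and an open list, and states no baseline adjustment for continuous outcomes that are measured at baseline. For correlations of 0.5 to 0.7, adjusting always would cut the SE by 13% to 29% against follow-up values, or by 13% to 8% against change scores. These figures rest on assumed correlations and equal variances at baseline and follow-up; the power figures also assume a 0.25 SD effect and 212 analysed per arm. The quantified loss concerns the continuous secondary outcomes. The document does not support a claim that the primary analysis is invalid or that its error rate is inflated. The change should be made because it is clear and cheap, but the trial does not stand or fall by it.

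**What to change.** 1. Delete the imbalance trigger. Keep the baseline table as description.
2. Analyse each continuous secondary outcome by ANCOVA, or a mixed model over the visits, with the baseline value and centre always included. State the outcome time point.
3. State that ANCOVA applies to continuous outcomes only. If 3P-MACE is to be covariate-adjusted, use a logistic or Cox model with a short list of prognostic covariates (for example age and prior infarction or stroke, with centre), fixed before unblinding.

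The cost is wording in the protocol and in the analysis plan, which the article says is still to be finalised. Baseline outcome values, demographics, medical history and site are already collected, so no new data, visits or patients are needed.

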### Current status

Patient recruitment for the trial is scheduled to commence in May 2025. The study protocol was successfully registered on ClinicalTrials.gov (https://register.clinicaltrials.gov) on April 2, 2025. The trial registration number is NCT06908473.

## Discussion

Driven by the high prevalence of MetS, its associated elevated cardiovascular and cerebrovascular risk, and the current lack of clarity regarding the effect of Tongmai Jiangtang Capsule—a glucose- and lipid-lowering agent—on cardiovascular events in MetS patients, there is an urgent need to fill the gap in high-level evidence for TCM compounds in this domain, prompting the initiation of this study. The adoption of a multi-center, double-blind RCT design represents the current “gold standard” for validating intervention efficacy. The multi-center design, by enrolling patients from diverse geographical regions (North, East, South, Southwest, Northwest China) and lifestyles (urban/rural), significantly enhances sample representativeness and reduces the “selection bias” inherent in single-center studies. Compared to other TCM studies, the multi-center nature of this trial better aligns with the characteristics of MetS, which involves “multi-system involvement and high population heterogeneity,” thereby strengthening the generalizability of the findings.

Notably, this study sets the primary endpoint as 3P-MACE (including non-fatal myocardial infarction, non-fatal stroke, and cardiovascular death). This “hard endpoint” directly reflects clinical outcomes and holds greater clinical significance compared to surrogate markers commonly used in traditional studies (39) [e.g., carotid intima-media thickness [IMT], flow-mediated dilation [FMD]]. The secondary endpoints encompass metabolic parameters and vascular-related indicators, addressing the developmental cascade of MetS: “metabolism-vascular injury-cardiovascular events.” This “stratified endpoint design” breaks through the limitation of traditional TCM research that often “emphasizes symptoms over hard outcomes,” better aligning with the core requirement of modern evidence-based medicine for demonstrating “clinical value.”

TJC has been marketed for years. Previous clinical trials and observational studies indicate that its adverse reactions are primarily mild gastrointestinal discomfort, with no reports of severe hepatic or renal impairment, ensuring good patient tolerability. Multiple clinical studies suggest that TJC can improve insulin resistance, effectively alleviate diabetic neuropathy and nephropathy, and improve prognosis in diabetic patients with cerebral infarction (32, 40).

The ten key pharmacologically active components in TJC, in order, are: quercetin, eugenol, campesterol, β-sitosterol, isofucosterol, stigmasterol, kaempferol, luteolin, isorhamnetin, and hederagenin. Among these, quercetin can effectively prevent and improve diabetic complications through multiple signaling pathways, including TNF-α, NF-κB, AMPK, AKT, and NRF2 (41–43). These pathways collectively contribute to anti-inflammatory and vascular protective activities (44, 45). β-sitosterol can enhance pancreatic β-cell function, increase insulin secretion and activity, effectively promote glucose uptake in adipocytes, and regulate fat synthesis and decomposition (46–48). Stigmasterol can promote glucose uptake in L6 cells *in vitro* and reduce fasting blood glucose and lipid levels in KKAy mice *in vivo*, alleviating insulin resistance and improving oral glucose tolerance (49–51). Kaempferol can upregulate the expression of genes and proteins related to the PI3K-AKT-GLUT4 signaling pathway in skeletal muscle, reduce blood glucose and body weight in KKAy mice, improve insulin resistance, and possesses significant anti-inflammatory activity (52–54). Eugenol's mitigation of cerebrovascular spasm may be related to inhibiting apoptosis and inflammatory responses within the basilar artery (55, 56). Stigmasterol, campesterol, and isofucosterol are all plant sterols, which can significantly reduce total cholesterol and LDL-C levels, increase HDL-C levels, and improve thickening of the aortic intima and media as well as smooth muscle cell migration (57–59). Meanwhile, quercetin, kaempferol, luteolin, and isorhamnetin are flavonols, possessing anti-inflammatory, antioxidant, cardiovascular, and neuroprotective effects (60–62). This suggests that beyond its established effects on improving insulin resistance and lowering blood glucose, TJC also has lipid-regulating, anti-inflammatory, and vascular compliance-improving properties, implying potential benefits for reducing cardiovascular risk. However, the actual clinical effect requires confirmation through high-quality RCTs.

If this study confirms that TJC significantly reduces the risk of cardiovascular and cerebrovascular events in MetS patients, its clinical significance will be manifold: Firstly, it will provide a new strategy for the “integrated traditional Chinese and Western medicine treatment” of MetS—addressing the shortcomings of current regimens in improving endothelial function and inhibiting chronic inflammation. Secondly, it will advance the “modern evaluation of TCM compounds"—using “high-level evidence” from RCTs to challenge the stereotype of “ambiguous efficacy of TCM” and provide evidence-based support for the clinical application of TCM compounds. Thirdly, it will contribute to the “Healthy China 2030” goals—by reducing the rate of cardiovascular events in MetS patients, decreasing healthcare resource consumption, and improving patients’ quality of life.

Even if the study results do not meet the primary endpoint (e.g., no significant difference in event rates between groups), the in-depth analysis of TJC's mechanisms of action (e.g., showing benefit only in subgroups with severe IR or high inflammatory burden) will provide important clues for subsequent formula optimization (e.g., increasing the dose of Astragalus to enhance AMPK activation) and conducting “precision intervention” studies (e.g., subgroup selection based on biomarkers such as HOMA-IR).

In conclusion, through its rigorous design, multi-dimensional endpoint setting, and scientific strategies for addressing challenges, this study is expected to provide high-level evidence for the prevention and treatment of cardiovascular and cerebrovascular events in MetS. Simultaneously, it offers a replicable “demonstration template” for the modern research and clinical application of TCM compounds. Its results are significant not only for the clinical value of TJC but also for providing crucial support for the national strategy of “Integrated Traditional Chinese and Western Medicine for Chronic Disease Prevention and Treatment.”

